|           | 5. Safety                                                                                      | 
 
Rates of hypotension (<100mmHg systolic or >20 mmHg systolic drop on standing)
 
Rates of adverse events
 
Rates of hyperkalaemia
 
                                                                           | 
 
Total occurrences
 
Total occurrences
 
                           |

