## 9.6. Subsequent Visits

Subsequent assessment will continue for both treatment arms for a further 36 months with follow up visits at weeks 1, 2, 4, 12, 26, and then every 13 weeks to 156 weeks. Windows either side of the visits will be two days for V1 and V2, 4 days at V3 and V4, 7 days for V5 and two weeks thereafter (all calculated from date of randomisation). Measurements at each follow-up visit will vary according to the schedule in Appendix B but will consist of a combination of:

- Office BP measurement, using a validated automated device;
- Venepuncture for creatinine & electrolyte levels;
- eGFR (MDRD and CKD-EPI estimations);
- Monitoring for side effects.
- Additional bloods for fasting blood sugar and HbA1c, BNP (where local labs allow), lipids, full blood count and samples for future analysis;
- QoL questionnaires;
- Issue of drug monitoring diary card.
- Urinalysis using albumin: creatinine ratio.
- Home blood pressure measurement recorded on diary card.

Patients will also be supplied with a validated home blood pressure monitoring machine, along with an additional diary card and an instruction sheet, for 1 week every 6 months to document their self-assessed blood pressures. They will take 2 readings twice daily, i.e. 2 each morning and 2 each evening over the

week. The readings for the first two days will be discarded and the mean of the remaining readings taken as the home blood pressure level.

Physicians will be strongly encouraged to manage blood pressure according to NICE CKD guidelines (2008): Blood Pressure Targets: CKD and ACR <70 mg/mmol: systolic blood pressure target of <140 mmHg (target range 120–139 mmHg) and diastolic blood pressure target <90 mmHg. Choice of antihypertensive agents: ACE inhibitors/ARBs if not already prescribed will be offered to people with hypertension and ACR ≥30 mg/mmol. We estimate that around two thirds of patients in BARACK D will be additionally taking an ACE inhibitor or ARB. The remainder, (people with CKD and hypertension and ACR <30 mg/mmol) will be offered a choice of antihypertensive treatment according to the NICE guidance on hypertension (NICE clinical guideline CG127 or its update) to prevent or ameliorate progression of CKD.

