### 11.4. Procedures for Reporting Adverse Events

All site staff are appropriately trained in the procedures to follow and the forms to use by the PC-CTU prior to study initiation. Regular central and on-site monitoring will be used to ensure that all adverse events are identified and acted on appropriately.

All adverse events will be recorded at trial visits for the initial 6 months of follow-up by the member of the

Research Team conducting that visit for the previous inter-visit period. Following this initial 6 month period, only the following AEs will be monitored by the member of the Research Team performing that visit. Safety concerns (i.e. significant decrease in eGFR (20% between visits, or 25% from baseline), rise in potassium levels (to above 5.5), and drop in BP (to below 100 in both arms))

- Enlargement of breasts in men and women
- Erectile dysfunction
- Irregular periods
- Vaginal bleeding after the menopause
- Deepening of the voice in women, change in the tone of voice in men
- Excessive hair growth
- Tiredness
- Palpitations
- Numbness and tingling

AEs considered related to the study medication as judged by a medically qualified member of the Research Team or the Sponsor will be followed until resolution or the event is considered stable, clinically insignificant or asymptomatic. All related AEs that result in a participant's withdrawal from the study or are present at the end of the study, should be followed up until a satisfactory resolution occurs.

It will be left to the recruiting physician's clinical judgment whether or not an AE is of sufficient severity to require the participant's removal from treatment and, if treatment is withdrawn, the reason will be recorded. A participant may also voluntarily withdraw from treatment due to what he or she perceives as an intolerable AE. If either of these occurs, the participant must undergo an end of study assessment and be given appropriate care under medical supervision until symptoms cease or the condition becomes stable.

- The severity of events will be assessed on the following scale: 1 = mild, 2 = moderate, 3 = severe.

The relationship of AEs to the study medication will be assessed by a medically qualified member of the Research Team.

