#### 2.2.3.4 TO DETERMINE THE SAFETY OF ARA IN PATIENTS WITH STAGE 3b CKD

##### Endpoints:

- (a) Rates of adverse events. All adverse events are recorded in the AE report CRF. The number of participants experiencing at least one AE and the number of AEs per participant will be reported. Number of SAEs will also be reported. Rates of hyperkalaemia:
- (b) Hyperkalaemia is defined as a potassium level  $\geq 5.5\text{mmol/l}$ . Potassium [K] is recorded at each visit. A binary variable will be derived as experiencing hyperkalaemia at any time point. Hyperkalaemia will be recorded as “yes” if the participant has potassium levels  $\geq 5.5\text{mmol/l}$  at any point during the study and “no” if at least one potassium measure is recorded and it does not meet the definition of hyperkalaemia. If a participant has hyperkalaemia at any point during the study, the maximum value of Hyperkalaemia for that patients will be used to derive a second variable to indicate whether the maximum hyperkalaemia was mild ( $5.5\text{-}5.9\text{mmol/l}$ ), moderate ( $6.0\text{-}6.4\text{mmol/l}$ ) or severe ( $>6.5\text{mmol/l}$ ).

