#### 2.2.5 SAFETY OUTCOMES

All adverse events during the first 6 months of follow-up including rates of hyperkalaemia will be recorded for the analysis of the safety profile of spironolactone in CKD. Following this initial 6 month period, **only the following AEs will be monitored by the member** of the Research Team performing that visit. Safety concerns (i.e. significant decrease in eGFR (20% between visits, or 25% from baseline), rise in potassium levels (to above 5.5), and drop in BP (to below 100 in both arms)).

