| 
 
• <5.5mmol/l
 
• 5.5-5.9mmol/l
 
• 6.0-6.4mmol/l
 
• >6.5mmol/l
 
 |                   |                 |         |
| Fisher's exact test (P-value)                                                                                                                |                   |                 |         |

Occurrence of adverse events and type of adverse events will be recorded in the variable AETERM. Number of adverse effects will be tabulated according to randomised group assignments and the proportions will be compared using Fisher's exact test. Instances of hyperkalaemia will be tabulated by treatment arm and proportions experiencing hyperkalaemia will be compared using Fisher's exact test.

TABLE 7 TYPE OF ADVERSE EVENTS BY GROUP

|                                | TREATMENT
(N=) | CONTROL
(N=) | OVERALL
(N=) |
|--------------------------------|-------------------|-----------------|-----------------|
| Number of events               |                   |                 |                 |
| Hyperkalaemia                  | N                 | N               | N               |
| Deterioration of renal disease | N                 | N               | N               |
| Hypotension        | N                 | N               | N               |
| Other adverse event:           | N                 | N               | N               |
| - Details                      |                   |                 |                 |
| Number of participants         |                   |                 |                 |
| Hyperkalaemia                  | N(%)              | N(%)            | N(%)            |

|                                   | TREATMENT
(N=) | CONTROL
(N=) | OVERALL
(N=) |
|-----------------------------------|-------------------|-----------------|-----------------|
| Deterioration of renal disease    | N(%)              | N(%)            | N(%)            |
| Hypotension                       | N(%)              | N(%)            | N(%)            |
| Other adverse event:
- Details | N(%)              | N(%)            | N(%)            |

Defined as <100mmHg systolic or >20 mmHg systolic drop on standing

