The safety analysis will focus on the adverse events. The safety population will include all participants who took at least one tablet of the study medication. Safety monitoring will invoke discontinuation rules for hyperkalaemia, deterioration of renal disease and hypotension. These will be recorded in the adverse event report form in the variable AETERM. These will be summarised by treatment arm as shown in table 11.

All adverse events (AEs) will be recorded at trial visits on the adverse event report form for the initial 6 months of follow-up by the member of the Research Team conducting that visit for the previous inter-visit period. Following this initial 6 month period, only the following AEs will be monitored by the member of the Research Team performing that visit in accordance with PC-CTU SOP TM19 "Pharmacovigilance": enlargement of breasts in men and women; erectile dysfunction; irregular periods; vaginal bleeding after the menopause; deepening of the voice in women, change in the tone of voice in men; excessive hair growth; tiredness; palpitations; and numbness and tingling.

All serious adverse events (SAEs) occurring during the study, either observed by the recruiting GP or reported by the participant, whether or not attributed to study medication, will be recorded on the CRF. The severity of adverse events will be assessed on the following scale: 1=mild; 2=moderate; 3=severe.

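### The any-adverse-event comparison has no time window, so it mixes six months of full recording with 30 months of a restricted list

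*Combined protocol and SAP*

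**What the plan says.** **Recording.** Protocol 11.4: "All adverse events will be recorded at trial visits for the initial 6 months of follow-up". After that, "Following this initial 6 month period, only the following AEs will be monitored by the member of the Research Team performing that visit". The restricted list has two parts: three laboratory or blood pressure concerns (eGFR fall, raised potassium, low blood pressure) and nine symptoms. Protocol 9.6 sets "follow up visits at weeks 1, 2, 4, 12, 26, and then every 13 weeks to 156 weeks", so the switch falls at V5. Serious AEs are recorded whatever their cause, from randomisation to 30 days after the last dose or last visit (protocol 11.5).

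**Analysis.** Protocol section 6 and SAP 1.4 list "Rates of adverse events" as a safety outcome with total occurrences as the timepoint. SAP 2.2.3.4: "The number of participants experiencing at least one AE and the number of AEs per participant will be reported". SAP section 8: "Number of adverse effects will be tabulated according to randomised group assignments and the proportions will be compared using Fisher's exact test". SAP Table 6 has one row for participants with any AE, followed by a Fisher test. SAP 8.1 and Table 8 test severity between arms and tabulate relatedness. None of these gives a window or a split at month 6.

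**The SAP's own lists.** SAP 2.2.5 states "All adverse events during the first 6 months of follow-up including rates of hyperkalaemia will be recorded", then names only the three laboratory or blood pressure concerns for the later period. SAP 8 and 8.5 give the later list as the nine symptoms only, beginning "enlargement of breasts in men and women; erectile dysfunction; irregular periods; vaginal bleeding after the menopause".

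**The concern.** A proportion with any AE has a clear meaning only if every participant-month is observed under one rule. Here an infection or a fall at month 3 counts and the same non-serious event at month 9 does not, while breast enlargement counts at both times. The pooled row therefore describes neither six-month nor three-year tolerability.

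The effect can run in two directions. If spironolactone raises listed events, dropping the unlisted background after month 6 makes the relative excess look larger than complete recording would show. If it raises a non-serious, unlisted event only after month 6, the row shows nothing. Participants and physicians know the allocation (protocol 9.4), so a short symptom list is also open to different reporting by arm.

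At stake is a headline AE percentage and P-value that readers would take as three-year tolerability.

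**Working it through.** **1. Share of follow-up under full recording.** Weeks: 26/156 = 16.7%. Visits: V1 to V5 of V1 to V15 = 5/15. The restricted rule covers the other 130 weeks and 10 visits.

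**2. Effect on the any-AE proportion.** The plan states no figure for this comparison, so there is none to reproduce. The documents give no AE rates, so everything below is an assumption shown as a range. Control rates per person-year are *a* for listed AEs (0.1 or 0.3) and *b* for unlisted non-serious AEs (0.3 or 1.0), constant over three years. Spironolactone multiplies listed events by 1.5 and leaves unlisted events unchanged.

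- As planned: P = 1 − exp(−(3*a* + 0.5*b*)), with 4.5*a* in place of 3*a* on spironolactone.
- Complete recording: P = 1 − exp(−(3*a* + 3*b*)), with the same replacement.

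Example, *a* = 0.1 and *b* = 0.3. Planned: 1 − exp(−0.45) = 36.2% control, 1 − exp(−0.60) = 45.1% spironolactone. Complete: 1 − exp(−1.20) = 69.9% and 1 − exp(−1.35) = 74.1%.

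| a | b | Planned, control / spironolactone | Difference | Complete, control / spironolactone | Difference |
|---|---|---|---|---|---|
| 0.1 | 0.3 | 36.2 / 45.1% | 8.9 | 69.9 / 74.1% | 4.2 |
| 0.1 | 1.0 | 55.1 / 61.3% | 6.3 | 96.3 / 96.8% | 0.5 |
| 0.3 | 0.3 | 65.0 / 77.7% | 12.7 | 83.5 / 89.5% | 6.0 |
| 0.3 | 1.0 | 75.3 / 84.3% | 8.9 | 98.0 / 98.7% | 0.7 |

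Risk ratios are 1.11 to 1.25 as planned and 1.01 to 1.07 under complete recording. The first six months alone give 1.03 to 1.21.

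**3. AEs per participant, which has no ceiling.** The planned ratio of mean counts is (4.5*a* + 0.5*b*)/(3*a* + 0.5*b*). In table order: 0.60/0.45 = 1.33, 0.95/0.80 = 1.19, 1.50/1.05 = 1.43 and 1.85/1.40 = 1.32. Complete recording gives 1.35/1.20 = 1.13, 3.45/3.30 = 1.05, 2.25/1.80 = 1.25 and 4.35/3.90 = 1.12. The absolute excess is 1.5*a* events per participant under both rules. Only the relative burden is distorted.

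**4. Late serious AEs.** Step 2 leaves them out. Suppose 20% to 40% in both arms have one after month 6. Each event-free proportion is multiplied by 0.8 to 0.6, and so is each difference. The planned range becomes about 5 to 10 points (at 20%) or 4 to 8 (at 40%), against 0.4 to 4.8 or 0.3 to 3.6 under complete recording.

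**5. A late unlisted non-serious harm.** If spironolactone multiplies only these events by 1.5, and only after month 6, the planned difference is 0.0 in all four cases. Complete recording would show 1.4 to 9.4 points.

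**6. No true effect and equal reporting.** The planned difference is 0.0 in every case.

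**7. The later lists side by side.**

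| Place | eGFR, potassium, BP events | Nine symptoms |
|---|---|---|
| Protocol 11.4 | kept | kept |
| SAP 2.2.5 | kept | not named |
| SAP 8 and 8.5, later list | not named | kept |

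SAP section 8 also says that hyperkalaemia, renal deterioration and hypotension go on the AE form, and Table 7 counts them. Under that section's own later list, those rows could not be filled after month 6. This conflict needs no assumed rate.

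**The case against.** The strongest reply is that the any-AE row is one output among several. Hyperkalaemia is derived from potassium at each visit, and hypotension from visit blood pressure and the discontinuation record, both across the whole study. Serious AEs have their own row, test and organ-class table. AEs by type and AEs leading to withdrawal are tabulated. SAP 2.2.3.2 already reports eGFR falls from laboratory values. All of this stands. A reader might infer that the whole safety objective rests on a distorted count, or that the trial cannot see late harms at all; the documents do not support either. The gap is limited to late, non-serious, unlisted events.

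Second, the same list applies to both arms, so narrowing it does not by itself tilt the result (step 6). That also stands. A reader might take the later list to be known spironolactone effects and conclude that the count must run against the drug. The documents do not label the nine symptoms that way, and tiredness, palpitations and eGFR decline are not specific. The condition is plausible, not established: the protocol's background cites perceived azotaemia and hyperkalaemia risk, and its rationale describes a blood pressure effect.

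Third, complete three-year recording approaches a ceiling and would itself hide an excess of listed events. This is fair for the proportions, but the count ratios in step 3 show the same direction without a ceiling.

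Fourth, pooling is inferred. SAP 2.2.5 links six-month recording to the safety-profile analysis. But it then adds later events and never limits the analysis, and total occurrences with no window leaves no other specified reading.

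Finally, secondary outcomes are declared exploratory (SAP 4.7). That lowers the stakes but does not give the row a meaning.

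**Conclusion.** The point holds for four outputs: any AE, AEs per participant, severity and relatedness. As written they combine two recording rules, with full recording for 16.7% of follow-up. Any distortion is conditional. It needs a true effect on listed events, or reporting that differs by arm, to overstate the relative burden. It needs a late, non-serious, unlisted harm to miss one.

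The size is illustrative only: 6.3 to 12.7 points as planned against 0.5 to 6.0 under complete recording, on constant assumed rates and a 1.5-fold effect on listed events, and smaller with late serious AEs included. The six-month risk ratio is not always the lower one: at *a* = *b* = 0.3 it is 1.21 against 1.20 pooled. The case for the six-month window is therefore that its meaning is clear, not that it always gives a smaller effect.

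Supplementary Table 1 shows more reproductive and breast events (6.4% v 0.7%) and more investigations events (59.0% v 41.4%) on spironolactone. A reader might take that as proof of a recording effect. It is not: its groups are 388 and 984, not the 677 and 695 of Supplementary Table 2, and it cannot separate a drug effect from a recording effect.

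The list conflict within the SAP holds without any assumption. The point does not touch the primary outcome. It is a cheap correction worth making.

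**What to change.** In SAP 2.2.3.4, section 8 and 8.1:

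- Restrict the all-AE comparison (number, severity, relatedness) to randomisation through week 26, by onset date, with the cut-off rule stated.
- Report each AE listed in protocol 11.4 separately by arm over 36 months.
- Keep the serious-AE analysis over 36 months.
- Do not test a pooled 36-month any-AE proportion. If it is shown, label it as mixed ascertainment.
- Align the later lists in SAP 2.2.5, 8 and 8.5 with protocol 11.4, so that the Table 7 rows can be completed.
- State as a limitation that non-serious, unlisted AEs after month 6 were not collected.

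The cost is SAP wording and re-cut tables. The AE listing in SAP 8.1 already holds onset dates, and the renal profile is scheduled at every follow-up visit in both arms. The downside is that there will be no single headline AE percentage for the whole trial.

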### **11.5. Reporting Procedures for Serious Adverse Events**

All SAEs occurring during the study, (from randomisation until 30 days following the last dose of trial medication/ last visit, whichever is the latter, either observed by the site physician or reported by the participant, whether or not attributed to study medication, will be recorded on the CRF and forwarded by the site to PC-CTU, using the "PC-CTU SAE Report Form" following assessment for seriousness and relatedness by the site clinician. This form will be completed and faxed or emailed to the PC-CTU using the details quoted on the report form. As a minimum, the following information will be recorded:

- Description
- Date of onset
- End date
- Severity
- Assessment of relatedness to study medication
- Other suspect drug or device
- Action taken

Follow-up information should be provided as necessary.

SAEs must be reported to the PC-CTU within 24 hours of discovery or notification of the event. The PC-CTU will acknowledge receipt of the SAE Report Form using the PC-CTU 'SAE Form Receipt' document. This receipt will be emailed or faxed to the site physician. If the site physician does not receive a receipt within 24hrs of them sending the report (during office hours), they should re-send the SAE Report Form to the PC-CTU by email or fax and telephone ahead.

The documentation will be reviewed by the Trial team. Following the initial check of the report, any additional information will be requested, and the CI or their medically qualified designated representative will review and evaluate the report for, causality and expectedness. In the event of a SUSAR the reporting timelines stated below will be followed. If there have been two assessments of causality made, the site physician's assessment cannot be downgraded. Where there is a discrepancy the worst case assessment is used for reporting purposes.

The PC-CTU will also ensure that SAE reports are reviewed by the Data Monitoring and Ethics Committee (DMEC), at their regular meetings.

Additional information, as it becomes available, will also be reported on the SAE Report Form (i.e. updating the original form) and returned to the PC-CTU by email or fax as above. The SAE Report Form will be filed in the Trial Master File according to PC-CTU\_SOP\_TM112 'Trial Master File and associated files', with copies filed in the patient's notes, the Case Record Form file and the Investigator Site File.

Any pregnancy occurring during the clinical trial and the outcome of the pregnancy will be recorded and followed up for congenital abnormalities or birth defects until the end of the trial at which point standard care will recommence.

Trial Managers log all SAEs reported. One of the metrics contained within this reporting is the number of SAEs reported and the cumulative number of SAEs for each study. Any concerns identified will be immediately raised with the Chief Investigator and may be tabled for discussion at the regular PC-CTU Management Committee meetings or referred to the study's DMEC for review. The DMEC also monitors the frequency and pattern of events reported as part of its independent oversight of the trial.

#### **11.5.1. Events exempt from immediate reporting as SAEs**

All SAEs will be reported to the PC-CTU from randomisation until 30-days after the participants' last dose/ last visit (as above)

#### **11.5.2. Procedure for immediate reporting of Serious Adverse Events**

- Site study team will complete an SAE report form for all reportable SAEs.
- The SAE report form will be scanned and emailed to the main trial team at the Primary Care Trials Unit, NDPCHS, Oxford immediately i.e., within 24 hours of site study team becoming aware of the event.
- Site study team will provide additional, missing or follow up information in a timely fashion.

